### Objectives

1.2

The primary objective is to implement and test a novel strategy to improve outcomes across the epilepsy care cascade marked by (1) retention in epilepsy care, (2) adherence to ASMs, and (3) seizure reduction with the measured goal of seizure freedom.

The first aim is to compare free ASMs vs. conditional cash using the epilepsy cascade of care. We hypothesize that the provision of free medication versus conditional cash will lead to (1) similar retention in epilepsy care—90% of PWE—at 360 days (Hypothesis 1a), (2) 80% of PWE regularly taking ASMs at 360 days (Hypothesis 1b), and (3) 65% of PWE achieving seizure freedom 360 days postenrollment (Hypothesis 1c).

The secondary aim is to detail facilitators and barriers to free medication versus conditional cash to improve seizure freedom among PWE. We hypothesize that barriers and facilitators to the uptake of each intervention strategy can be learned through careful, structured documentation by healthcare workers during study visits using an investigator‐designed written intake form as well as free‐text responses, serving as foundational information for a future larger‐scale implementation study in low‐resource populations.

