## STATISTICAL METHODS

6

We choose a randomized two‐arm design with an equal sample size in the arm with the provision of conditional cash and the arm with the provision of free medication. Our sample size calculation is based on Hypothesis 1a.

To investigate Hypothesis 1a, we will first test the null hypothesis that the retention rate of the group with the provision of conditional cash is less than or equal to 90% using a non‐inferiority one‐sample proportion test. We will then test the null hypothesis that the provision of conditional cash will lead to a retention rate no less than the retention rate of free medication (controlling for medication type) using a noninferiority two‐sample proportion test. Since there are two hypotheses, in the sample calculation, we applied the Bonferroni correction to ensure a familywise error rate of 0.05.^27^ Given the existing studies and preliminary results, we expect that the retention rate of the group with the provision of conditional cash will have a retention rate higher than 90%. This reflects financial incentive clinical trials in other diseases where the intervention improves retention in care, particularly studied in HIV/AIDS.^28^, ^29^

Assuming it is 90%, to ensure a statistical power of 80%, with a noninferiority margin of 8.5%, the sample size of the arm with the conditional cash required is 98.^30^ We will then test the null hypothesis that the provision of conditional cash will lead to a retention rate no less than the retention rate of free ASMs using a noninferior two‐sample proportion test. Assuming the conditional cash group has 90% of PWE who will return at 12 months, with a noninferiority margin of 12%, to ensure statistical power of 80%, the sample size of the arm with the conditional cash required is 99.

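### The null of the between-arm retention test for Hypothesis 1a is worded in reverse and without its 12-point margin, contradicting the plan's own non-inferiority label and sample size

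*Protocol article*

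**What the plan says.** All of this stands in the Statistical methods section (section 6) of the protocol article unless noted.

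- The between-arm test for Hypothesis 1a is introduced with the "null hypothesis that the provision of conditional cash will lead to a retention rate no less than the retention rate of free medication", with an adjustment for medication type mentioned in brackets. The test is named as a non-inferiority two-sample proportion test.
- The next paragraph repeats it as the "null hypothesis that the provision of conditional cash will lead to a retention rate no less than the retention rate of free ASMs", again under a non-inferiority label.
- Neither statement of the null contains a margin. A 12% margin appears in the sentence after the second statement, as an input to the sample size: "Assuming the conditional cash group has 90% of PWE who will return at 12 months", the section gives the margin and then concludes "to ensure statistical power of 80%, the sample size of the arm with the conditional cash required is 99".
- On error control: "Since there are two hypotheses, in the sample calculation, we applied the Bonferroni correction to ensure a familywise error rate of 0.05".
- The design is randomized "with an equal sample size in the arm with the provision of conditional cash and the arm with the provision of free medication".
- The other nulls in the section run the opposite way. The one-sample null for 1a is retention at or below 90%. The two-sample nulls for 1b and 1c are cash at or below free medication.
- Objectives (section 1.2) gives Hypothesis 1a as similar retention in the two arms, at 90%, at 360 days.

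**The concern.** A non-inferiority test puts the unwanted state in the null (the new strategy is worse by the margin or more) and claims non-inferiority by rejecting it. Here the wanted state, cash at least as good as free medication, is the null. Under that wording the only conclusion a significant result can support is that cash retention is lower. The hoped-for conclusion could be reached only by failing to reject, which is not evidence for it and becomes easier as the data become weaker.

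This is the only between-arm proportion test given for Hypothesis 1a, and that hypothesis determines the sample size. The null is also the sentence that an analyst implements and against which a reader checks the result. The reversal occurs in both statements of the test, so it could be carried unchanged into later documents.

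**Working it through.** **1. Which null does the stated sample size belong to?**

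Inputs:
- Cash retention 90% (section 6).
- Free-medication retention 90%. Section 6 does not state it; it is taken from the similar-retention hypothesis in section 1.2.
- Margin 0.12 and power 80% (section 6), so z = 0.8416.
- Alpha 0.05 / 2 = 0.025 by Bonferroni (section 6). The article does not say one-sided; this is assumed because the test is non-inferiority. z = 1.960.
- Equal allocation (section 6).

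For H0: p(cash) − p(free) ≤ −0.12, with unpooled variance:

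n per arm = [0.9 × 0.1 + 0.9 × 0.1] × (1.960 + 0.8416)² / 0.12² = 0.18 × 7.849 / 0.0144 = 98.1, rounded up to **99**.

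This is the stated figure. One-sided alpha 0.05 gives 78 and 0.0125 gives 119, so neither alternative fits. The companion one-sample figure reproduces at the same alpha: 0.09 × 7.849 / 0.085² = 97.8, rounded up to **98**. The calculation therefore uses the conventional non-inferiority null, with its margin, and not the null in the text.

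**2. What would the written null do if applied literally?**

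The written null is H0: p(cash) ≥ p(free). It is taken here as a pooled z test at one-sided 0.025, rejecting when cash is significantly lower. The comparison is the correctly stated test with a 12-point margin. Probabilities come from full enumeration of two binomials with 100 per arm (200 participants randomized 1:1, section 1.1) and free medication at 90%.

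| True cash retention | Written null not rejected | Correct null: non-inferiority claimed, score test | Correct null: non-inferiority claimed, unpooled test |
|---|---|---|---|
| 78% (on the margin) | 34.7% | 2.5% | 2.8% |
| 82% | 62.4% | 12.4% | 13.8% |

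The second column is a false claim of non-inferiority only if someone treats non-rejection as success.

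**3. Does correcting the null preserve the stated power?**

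Exact power at 90% in both arms, margin 12 points, one-sided 0.025:

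| Test of the corrected null | 99 per arm | 100 per arm |
|---|---|---|
| Unpooled variance (matches the sample-size formula) | 80.4% | 81.3% |
| Score test (Farrington–Manning) | 76.4% | 78.1% |

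The stated 80% holds with the unpooled method and is missed by about 2 to 4 points with a score method.

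**The case against.** The strongest reply is that this is a slip in wording. The label, the margin, the alpha and the sample size all agree on the standard test, and only the verbal null is out of line. A statistician reading the paragraph would recover the intention. That is correct, and it limits the point: the design is sound and the margin is not missing from the plan, only from the null. It does not remove the point, because the null is stated explicitly, twice, and contradicts the rest of its own section. Condensing a protocol into an article can drop detail, but it does not reverse a hypothesis.

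Two stronger readings are tempting, and the document does not support either.

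- *That the trial will declare non-inferiority when the test fails to reject.* No passage says so, and the procedure named is a non-inferiority test. The 35% is a worst case under literal application, not the plan's expected error rate.
- *That power collapses from 80% to 2.6%.* With both arms at 90% the written test does reject 2.6% of the time, but the written null is then true. The 2.6% is that test's type I error, and setting it against the 80% power of a different test does not compare like with like.

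It is also fair to say that the choice of interval method may be left to a statistical analysis plan. The correction therefore need not impose a score interval.

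**Conclusion.** The point holds as an error in the stated hypothesis, not in the design. The between-arm null for Hypothesis 1a is reversed and lacks its margin in both places, and it contradicts the non-inferiority label, the 12% margin, the 99 per arm and the direction of the 1b and 1c nulls. As written, rejection would show that cash is worse, and no rejection could establish non-inferiority.

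The size of the risk is conditional. If the null were applied literally and non-rejection were taken as success, cash that is truly 12 points worse would pass about 35% of the time, against 2.5% to 2.8% for the correctly stated test. This assumes 90% retention on free medication, 100 per arm, one-sided 0.025 and a pooled z test for the written null. The contradiction itself needs none of these assumptions. The match with 99 does rest on 90% in both arms and on the one-sided 0.025.

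It should be corrected before analysis: it concerns the hypothesis that sizes the trial, and the correction is cheap.

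**What to change.** In both places in section 6, restate the hypotheses as H0: p(cash) − p(free ASM) ≤ −0.12 against H1: p(cash) − p(free ASM) > −0.12, at one-sided alpha 0.025. Add the decision rule: non-inferiority is declared only if the lower limit of the two-sided 95% confidence interval for the difference lies above −12 percentage points.

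Edit the null rather than replacing the whole sentences, so that the adjustment for medication type in the first statement is kept.

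Use an interval method consistent with the sample-size formula (unpooled variance, about 80% to 81% power at 99 to 100 per arm). If a score interval is preferred, restate the power as about 76% to 78%.

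The cost is a change of wording, plus a revised power statement if a score interval is chosen. Sample size and data collection do not change.

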### Study setting

2.1

The Ignace Deen Hospital is one of two teaching hospitals in Conakry, receiving several thousand cases of epilepsy per year. Additional recruitment and enrollment are planned to occur in Kankan, Forecariah, and Dubreka regional health facilities. There are five practicing neurologists in Guinea. Table 1 displays summary statistics from a prior cohort study we conducted with 297 Guinean PWE whose characteristics are expected to resemble future trial participants.

**TABLE 1 epi412889-tbl-0001:** Epilepsy patients, Republic of Guinea (*n* = 297).

	Female (*n* = 159)	Male (*n* = 138)	Children (<18 years, *n* = 148)	Adults (> = 18 years, *n* = 149)	Full cohort (*n* = 297)
Mean age (years; range)	20.4 (1–66)	18.6 (0.8–62)	8.5 (0–17)	30.5 (18–66)	19.6 (0.8–66)
Highest education (*n*)					
No school	35	32	48	19	67
Primary school	52	50	72	30	102
Middle school	23	21	18	26	44
High school	17	17	5	29	34
University	30	15	1	44	45
Was water unavailable for at least 1 day in the past 2 weeks? (% yes)	47	37	40	44	43
Has previously taken ASMs (% yes)	89	78	84	84	84
Currently taking ASMs (% yes)	70	54	60	65	63
Annual mean household income per capita (USD)	639	924	603	975	770
Duration of epilepsy, years (mean)	7.6	7.2	3.5	11.1	7.4
Seizure frequency in past month (mean)	3.0	4.1	4.1	2.8	3.5
Ever injured due to seizures (% yes)	58	51	35	74	55
Ever used non‐allopathic treatments (*n*)					
Traditional medicine	92	70	78	84	162
Prayer	29	26	29	26	55
Special diets	16	3	4	15	19
ASMs ever taken (*n*)					
Carbamazepine	70	51	44	77	121
Benzodiazepine	6	7	6	7	13
Levetiracetam	28	19	29	18	47
Phenobarbital	60	33	41	52	93
Phenytoin	0	1	0	1	1
Sodium valproate	58	35	58	35	93
Other ASM	10	11	5	16	21
Previous brain imaging (% yes)					
CT	42	33	37	38	38
EEG	49	49	55	42	49
MRI	5	2	4	3	4

*Note*: Gray shades denote the title of the columns.

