### Informed consent

2.3

Screening will be performed by Guinean investigators with mentorship and collaboration with the U.S. team (Appendix S1) and will include a brain MRI to rule out other diagnoses (e.g., tumors, untreated significant hydrocephalus). An estimated 50% of the enrollment will occur in Conakry and 50% at rural and peri‐urban sites.

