For Hypothesis 1b, we will use a one‐sample proportion test to test the null hypothesis that the percentage of PWE regularly taking ASMs at 12 months in the conditional cash arm is less than or equal to 85%, and we will use a two‐sample proportion test for the null hypothesis that the percentage of PWE regularly taking ASMs in the conditional cash arm is less than or equal to the percentage of PWE regularly taking ASMs in the free medication arm. For Hypothesis 1c, we will use a one‐sample proportion test to test the null hypothesis that the percentage of PWE with seizure freedom at 12 months in the conditional cash arm is less than or equal to 65%, and we will use a two‐sample proportion test for the null hypothesis that the percentage of seizure freedom in the conditional cash arm is less than or equal to the percentage of seizure freedom in the free medication arm.

To leverage the longitudinal observations collected during follow‐up visits at 90, 180, 270, and 360 days, we will use a generalized linear mixed effects model which allows us to study the association between multiple baseline variables (e.g., including the intervention options, education level, medication status, ASM type, distance to the study clinics) while accounting for the correlation between longitudinal observations.

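### The between-arm retention test names only medication type as a control and leaves out site and distance, a small missed gain in precision

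*Protocol article*

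**What the plan says.** **The test.** Statistical Methods sets a two-sample non-inferiority proportion test for Hypothesis 1a, on whether conditional cash "will lead to a retention rate no less than the retention rate of free ASMs". I read this as the usual non-inferiority comparison. The test is described twice. The first description names medication type as a control; the second names none. The sizing statement uses a 12-point margin and 80% power. Its retention assumption reads "Assuming the conditional cash group has 90% of PWE who will return at 12 months", and it concludes that "the sample size of the arm with the conditional cash required is 99". On multiplicity, "we applied the Bonferroni correction to ensure a familywise error rate of 0.05".

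**Where participants come from.** Study Setting places the trial at a Conakry teaching hospital and adds: "Additional recruitment and enrollment are planned to occur in Kankan, Forecariah, and Dubreka regional health facilities". The Informed Consent section says: "An estimated 50% of the enrollment will occur in Conakry and 50% at rural", where the second half also covers peri-urban locations.

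**Where site and distance appear.** The longitudinal mixed model at the end of Statistical Methods lists, as examples of baseline variables, the intervention and "education level, medication status, ASM type, distance to the study clinics". Distance is named there and in no other analysis. Site is named in no analysis.

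**Medication type.** Under Intervention Description, the neurologist chooses the drug in light of the patient's history. Under the choice of comparators, the cash arm receives a drug recommendation and purchasing advice rather than the drug itself.

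**The concern.** Retention means physically coming back to a clinic, so where a participant enrolled and how far they must travel are natural candidates to predict it. The article points the same way. It sets the cash amount partly against the cost of a return journey, allows a visit window partly for public transport, and lists distance as a variable of interest. Yet the comparison that gives the larger of the two sizing figures (99, against 98 for the one-sample test) uses neither variable.

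The one control it does name is a weak choice. The neurologist selects the drug, and the article does not say that this happens before randomisation, so medication type is not clearly a baseline variable. A plain two-sample proportion test also has no place for a covariate. Site and distance are better candidates, since neither depends on the assigned arm.

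What is at stake is precision. If site or distance predicts return, the unadjusted interval for the risk difference is somewhat wider than it need be, in a design with little power to spare.

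**Working it through.** **Inputs from the article:** familywise error 0.05 over two hypotheses; 80% power; 12-point margin; 90% retention with conditional cash; 1:1 allocation of 200, so 100 per arm; half of enrolment in Conakry.

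**Inputs assumed:** 90% retention with free medication (Hypothesis 1a speaks of similar retention); one-sided 0.025 per test, which is not written out but follows from 0.05/2 and reproduces the stated sizes; retention by site and the effect of distance, for which the article gives no figures.

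**Step 1: reproduce the plan.** Here (1.960 + 0.842)² = 7.849.

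- Two-sample: n = 2 × 0.90 × 0.10 × 7.849 / 0.12² = 98.1, rounded up to **99**. (One-sided 0.05 would give 78, and 0.0125 would give 119.)
- One-sample, margin 8.5 points: n = 0.09 × 7.849 / 0.085² = 97.8, rounded up to **98**.

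Both match with no covariate in the variance. At 100 per arm, SE = √(2 × 0.09 / 100) = 0.0424. Power = Φ(0.12 / 0.0424 − 1.96) = 80.7%, and the 95% CI half-width is 8.3 points.

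**Step 2: adjust for site.** With a 50:50 split, 90% overall and a gap d between sites, the mean within-site variance is 0.09 − (d/2)². This replaces 0.09 above.

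| Assumed retention, Conakry/regional | Variance | Change | n per arm | Power at 100 per arm | CI half-width (points) |
|---|---|---|---|---|---|
| 90/90 | 0.0900 | 0 | 99 | 80.7% | 8.3 |
| 92.5/87.5 | 0.0894 | −0.7% | 98 | 81.0% | 8.3 |
| 95/85 | 0.0875 | −2.8% | 96 | 81.8% | 8.2 |
| 97/83 | 0.0851 | −5.4% | 93 | 82.9% | 8.1 |
| 98/82 | 0.0836 | −7.1% | 92 | 83.5% | 8.0 |

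The limit is 100/80, the widest gap compatible with 90% overall: power 85.1%, n = 88.

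**Step 3: check by simulation.** With 100,000 replicates and a site-standardised difference, power (unadjusted against adjusted) is 81.1% against 80.9% at 90/90, 81.2% against 82.1% at 95/85, and 81.2% against 83.7% at 98/82. Type I error at the margin is about 2.8 to 2.9% for both. A site-stratified Mantel-Haenszel difference gives 81.1% against 81.9% at 95/85 and 81.2% against 83.4% at 98/82.

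**Step 4: add distance.** These figures use 3,000 simulated trials per scenario and standardised logistic regression.

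- Sites 94/86, odds ratio 0.5 per SD of distance: power 80.8% unadjusted, 82.8% adjusted. The large-sample variance falls 6.5%, giving 83.3%.
- Sites 96/84, odds ratio 0.41 per SD: 81.3% and 84.9%. The large-sample variance falls about 12%, giving about 85%.

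**Step 5: chance imbalance in site mix.** If randomisation is not stratified, the SD of the between-arm difference in site share is √(2 × 0.25 / 100) = 0.071. With a 10-point site gap this contributes (0.10 × 0.071)² = 0.00005 to the variance. Divided by 0.0018, that is 2.8%, the same 2.8% shown for 95/85 in step 2.

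**The case against.** The strongest reply is that nothing here is wrong. Under randomisation the unadjusted test is valid and reaches its planned power. The article condenses a fuller protocol, and covariates are commonly settled in an analysis plan that is not shown. This stands as far as it goes: silence on covariates would be no finding. But the article does name the test and one control for it, and that choice can be improved with variables fixed before randomisation.

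A reader might infer more than the documents support:

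- **That the trial is undersized.** It is not on this account; 99 reproduces exactly.
- **That the plan overlooks distance.** Distance is in the mixed model, and that list is given as examples, so it does not show that site was excluded there.
- **That access is known to differ by site.** This is inferred from the urban and rural mix. The article reports no difference in access or retention by site.
- **That chance site imbalance is a second harm.** It is how site variation enters the unadjusted variance (step 5), so the confidence interval already covers it.
- **That adjustment is free.** In the most favourable distance scenario, simulated type I error was 0.030 adjusted against 0.025 unadjusted, with Monte Carlo SE 0.003. Inflation is neither shown nor excluded. A true shift of that size would by itself raise power from about 80.7% to 82.8%, so the 84.9% simulated there is best read as an upper figure.

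Two practical cautions also stand. At 90% retention only about 200 × 0.10 = 20 participants are expected not to be retained. Arm, distance and four separate locations would then mean five terms on about 20 events. And the schedule of tests has no distance item, while the enrolment survey in Appendix S2 is not shown, so complete capture of distance is likely but not confirmed.

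**Conclusion.** The point holds as a small missed efficiency and an optional improvement. For site alone, the gain at 100 per arm is about 0 to 3 power points, or 0 to 7 participants per arm, over assumed splits from 90/90 to 98/82. Power might reach about 85% if distance is also strongly prognostic. All of these sizes rest on assumed site and distance effects, 90% retention in both arms and a one-sided 0.025 test. If neither variable predicts return, there is no gain.

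**What to change.** Before unblinded outcome data are seen, prespecify the Hypothesis 1a between-arm risk difference and its confidence interval in one of two forms:

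- a Mantel-Haenszel difference stratified by site in two levels, Conakry against regional, which suits the small number of expected non-retained participants; or
- a risk difference standardised from a logistic regression on arm, two-level site and baseline distance, after confirming that distance is recorded at baseline for everyone.

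Keep the 12-point margin and the sample size. Report the unadjusted test as a sensitivity analysis and add site to the mixed model.

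The cost is analysis wording and a slightly more complex analysis; no participants or visits are added.

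### Retention has a non-inferiority test between arms but no pre-specified superiority step after it; adding one costs no alpha, patients or data

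*Protocol article*

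**What the plan says.** Objectives states Hypothesis 1a for free medication versus conditional cash as "similar retention in epilepsy care—90% of PWE—at 360 days (Hypothesis 1a").

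Statistical Methods bases the sample size on this hypothesis and names two tests of retention:

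- a one-sample test of the cash arm against 90%, with a margin of 8.5 points and 98 participants;
- a comparison with "the retention rate of free medication (controlling for medication type) using a noninferiority two‐sample proportion test", sized as follows: "Assuming the conditional cash group has 90% of PWE who will return at 12 months, with a noninferiority margin of 12" points; "to ensure statistical power of 80%, the sample size of the arm with the conditional cash required is 99".

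On error control, "we applied the Bonferroni correction to ensure a familywise error rate of 0.05" across these two hypotheses.

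On what is expected of cash, the section says "we expect that the retention rate of the group with the provision of conditional cash will have a retention rate higher than 90"%, and supports this with "This reflects financial incentive clinical trials in other diseases where the intervention improves retention in care".

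For Hypotheses 1b and 1c the same section writes the between-arm null as cash being no better than free medication, which is a superiority-type null. No such null is given for retention. The section also plans a longitudinal generalized linear mixed model with the intervention among its covariates. It does not name the outcome of that model and describes its aim as studying association.

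**The concern.** The payment is made for attending visits (Intervention description), and attendance is the nominated primary outcome (Outcomes). The plan nevertheless provides a superiority-type comparison for the two outcomes that the payment does not directly reward, and none for retention. If the cash arm retained clearly more people, the only pre-specified between-arm conclusion on retention would be that cash is not worse by 12 points or more. A statement that cash retains more people would then be post hoc, although the same data and the same interval could have supported it as a planned conclusion.

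**Working it through.** **Inputs.** From Statistical Methods: 90% retention with cash, margin 0.12 (two-sample), margin 0.085 (one-sample), power 80%, familywise error 0.05 split by Bonferroni over two hypotheses, giving 0.025 each. From Trial design: 200 participants randomized 1:1, so 100 per arm. Two inputs are assumptions. The free-ASM rate is not stated in the sizing sentence and is taken as 90% from Hypothesis 1a. The sidedness of the 0.025 is not stated and is inferred from step 1.

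**Step 1: reproduce the plan's figures.** With z(0.975) = 1.960 and z(0.80) = 0.842, (1.960 + 0.842)² = 7.849 (from unrounded quantiles).

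- One-sample: n = 7.849 × 0.90 × 0.10 / 0.085² = 97.8, so 98, as stated.
- Two-sample: n = 7.849 × (0.09 + 0.09) / 0.12² = 98.1, so 99 per arm, as stated.

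One-sided 0.05 gives 78 and 78, and one-sided 0.0125 gives 119 and 119. Of the levels tried, only one-sided 0.025 with equal 90% rates reproduces both figures.

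**Step 2: why the extra step costs no alpha.** Let d be cash retention minus free-ASM retention. The non-inferiority null is d ≤ -0.12 and the superiority null is d ≤ 0. The first lies inside the second. If superiority is tested only after non-inferiority is shown, both can use the same one-sided 0.025. Read from one 95% interval, a lower limit above 0 is necessarily above -0.12. Exact binomial enumeration at 100 per arm confirms this: the probability of superiority without non-inferiority is 0. With 90% in both arms, superiority is falsely declared with probability 0.026, against a nominal 0.025. The small excess comes from the normal approximation.

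**Step 3: what the step would deliver.** Exact binomial enumeration at 100 per arm. Superiority is a pooled z statistic above 1.96; non-inferiority is an unpooled 95% lower limit above -12 points. The true rates are illustrative.

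| Free ASM | Cash | Non-inferiority power | Superiority power |
|---|---|---|---|
| 90% | 93% | 0.97 | 0.12 |
| 90% | 95% | 0.996 | 0.27 |
| 90% | 97% | >0.999 | 0.53 |
| 90% | 99% | >0.999 | 0.85 |
| 85% | 95% | >0.999 | 0.68 |
| 75% | 90% | 0.999 | 0.82 |
| 80% | 95% | >0.999 | 0.92 |

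Reading superiority from the unpooled interval instead changes these values little (0.28 at 95% versus 90%, 0.56 at 97% versus 90%).

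**Step 4: the observed result needed.** The lower limit is d - 1.96 × √[p_c(1 - p_c)/100 + p_f(1 - p_f)/100], where p_c and p_f are the observed cash and free-ASM proportions. With 90/100 retained on free ASMs, 97/100 on cash gives 0.07 - 1.96 × √(0.000291 + 0.0009) = 0.002, just above 0. With 96/100 the limit is -0.010. So 97% is the smallest observed cash rate that would show superiority in that case.

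**The case against.** The strongest reply is that non-inferiority is what the hypothesis calls for. Hypothesis 1a predicts similar retention, the sample size is built on it, and 99 reproduces with equal rates. The authors wrote superiority-type nulls for 1b and 1c, so the choice for 1a looks deliberate. All of this stands, and non-inferiority should remain the first test.

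Three stronger readings are tempting, and the document does not support them.

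- A reader might infer that the plan expects cash to beat free ASMs. It expects cash to exceed a fixed 90% benchmark, and cites the incentive trials in support of that. The aim to "test a novel strategy to improve outcomes across the epilepsy care cascade" describes the overall strategy. The comparator is itself an active intervention, so incentive trials in other diseases need not predict superiority over free drugs.
- A reader might infer that a benefit could be reported only as cash being not much worse. Nothing prevents reporting the estimate with its interval, which would show the direction and size of a benefit. The mixed model also includes the intervention, although its outcome is not named.
- A reader might infer that superiority on retention is the trial's main question and goes unanswered. The stated first aim is to compare the arms, with similarity hypothesised for retention.

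It can also be said that the order of testing belongs in the analysis plan, which is not shown and could already contain this step. That carries some weight. However, the article itself fixes the retention tests, the margins and the alpha split, and gives the superiority-type nulls for 1b and 1c next to them.

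Finally, at the plan's own 90% for free ASMs the step would usually fail for modest gains. That is correct, and it limits the benefit of the change. It does not give the change a cost.

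**Conclusion.** The point holds as a free improvement, not as an error in the design. Non-inferiority suits Hypothesis 1a, and the stated 98 and 99 are correct at one-sided 0.025. What is missing from the tests named for retention is a pre-specified confirmatory step that would let the trial conclude that cash retains more people, if the data show it.

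The gain is modest under the plan's assumptions. With free ASMs at 90%, superiority power at 100 per arm is 0.12 to 0.53 for cash between 93% and 97%, and reaches 0.85 only at 99%. The step is worth most if 90% is optimistic for the free-ASM arm: 0.68, 0.82 and 0.92 in the three scenarios with free-ASM retention of 85%, 75% and 80%. These figures assume 100 analysed per arm, a binary retention outcome at 360 days and one-sided 0.025. The true rates are illustrative and do not come from the protocol.

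**What to change.** Add to Statistical Methods, under Hypothesis 1a:

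*The difference in 360-day retention (conditional cash minus free ASM) will be reported with its two-sided 95% confidence interval. Non-inferiority is concluded if the lower limit is above -12 percentage points. Only if non-inferiority is concluded will superiority be assessed; it is concluded if the lower limit is also above 0. Both are tested at one-sided 0.025, with no further adjustment.*

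Add a sentence stating that the trial is sized for non-inferiority and that superiority power at 100 per arm is limited (about 0.27 at 95% versus 90%, and 0.53 at 97% versus 90%), so that failure to show superiority is not read as evidence of no benefit.

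The cost is a few sentences, with no change to sample size, data collection or alpha. The step must be fixed before between-arm outcome data are seen. If the analysis plan already contains it, the two documents need only be aligned.
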